### Recruitment

A nurse at the PCC will pre-screen potential study participants from an electronic patient register system according to age and the excluding medical conditions. After identification, the nurse will send letters to potential participants, including an invitation to participate in the study. The potential participants will be asked to answer whether they are interested in taking part either by calling a contact number, answering through a letter or sending an e-mail. Posters and brochures about the study will be placed at the PCC and clinical staff will be asked to inform any potential older adult about the study. After receiving contact information for potential participants, a research assistant will call to inform them about the project and go through the eligibility criteria. If the participant meets the criteria, the research assistant will book a time for a home-visit. In this visit, the research assistant will provide oral and written information about the study and will ask for written consent. If the participant will meet all the eligibility criteria, and will obtain the written consent, he/she will be enrolled in the POSITIVE study. After the participant is enrolled, she/he will be randomised into the study.

### Randomisation

A computerised stratified randomisation technique will be applied in each of the study groups (CG and IG) based on age group (70–85, > 85), history of cognitive impairment and history of stroke to guarantee the existence of comparable groups. These factors have been significantly associated with frailty and pre-frailty status [32, 33]. To ensure objectiveness, the randomisation and allocation will be done by a person in the research team who will not be involved in the screening process.

### Interventions

#### Multimodal interventions

The participants will be randomised into one of the two groups and the interventions will be delivered in the participants’ homes. The duration of the intervention period is 6 months, at baseline, after 3 and 6 months into the intervention for both the control (CG) and the intervention group (IG). The time schedule for the study interventions is shown in Fig. 2.

Both the CG and the IG will receive a medical review via the PCC to ensure that the study participants follow appropriate medication. Furthermore, all participants will receive generic nutritional recommendations and physical exercise program according to the Vivifrail prescription guide [34]. Since the abovementioned interventions have evidence in improving frailty status [6–11], both treatment arms will receive these interventions, and this study can focus on the evaluation of the impact of using the POSITIVE technical solution to support the intervention.

The Vivifrail program is divided into six different exercise program levels, according to different functional levels and level of frailty, and possible risk of falls. The exercises include cardio exercise such as walking, strength and balance exercises and stretching. All participants will receive a program which is prescribed according to their functional level. In terms of improvement in the condition, a participant can continue to follow Vivifrail program according to a higher functional level or the program for robust persons until the end of the study. The programs and recommendations will be introduced and handed out by the research assistant at baseline. All participants will have the opportunity to call a physiotherapist in case they have questions or doubts considering the training according to Vivifrail. Furthermore, they can visit the PCC whenever they need during the follow-up, as a part of the standard care.

#### POSITIVE home monitoring system

The IG will receive the POSITIVE system (see Fig. 3), which will monitor the intrinsic capacity of the participants through a monitoring kit including physical tests and questionnaires, as well as compliance to the Vivifrail exercises, which are supposed to be performed at home. The interaction with the home monitoring system is handled by a mobile application that acts as a guiding element to the older person. The application works also as a data concentrator input point, not only enabling the older adult using the sensors, but also completing a set of questionnaires to enrich the information handled by the clinical professionals.

**Fig. 3 Fig3:**
[figure not shown]
The POSITIVE system and its different components and users

Results from physical tests will be automatically registered in the platform once the sensors send the data to the tablet via Bluetooth. These sensors include a gait speed placed on the floor (does not measure steps), a device to measure power in the lower limbs by monitoring the chair stand test, which will be placed on the thigh, and a smart weight scale to track involuntary weight loss (See Fig. 4).

**Fig. 4 Fig4:**
[figure not shown]
The POSITIVE mobile measurement devices

Finally, adherence to the physical activity program is also measured by monitoring access through the app. The system will aim to prevent disability by triggering timely interventions if early decline in functional capacity is detected. Further, the system will provide nutritional recommendations depending on the participants’ health profile (generic, diabetic, obese, malnourished), which in turn can have an impact in vitality [21]. Additionally, the system will enable written communication between the older adult and a health care professional through the POSITIVE application.

The home monitoring system that belongs to the POSITIVE system will be installed and introduced by a researcher from the Royal Institute of Technology (KTH). The nurse connected to the PCC will remotely monitor the participants in the IG through the technology provided with the home monitoring system. During the 6-month follow-up period, if the system detects functional decline, the nurse will receive alerts from the system and will contact the participant to perform required interventions and, if needed, consult with the general practitioner (GP) responsible for the participants to plan interventions. The nurse will be recommended to consult the GP if she/he detects worsening in frailty status. The POSITIVE platform will even provide decision-making support for GPs and can give guidance on the need to refer the patient to specialised care. Further medical interventions required in primary care may include medical adjustments, updating the participants’ functional level in the POSITIVE platform and adjusting the Vivifrail program to their functional level, and referral of the patient to specialised care.

### Data collection

A technical researcher from KTH will collect data received from the POSITIVE platform. The server for the POSITIVE platform will be provided by Amazon Web Services. This service meets General Data Protection Regulation (GDPR) requirements [35] in terms of security and encryption of personal data, ability to restore the availability and access to personal data in a timely manner in the event of a physical or technical incidence. It also meets requirements for regularly testing, assessing and evaluating the effectiveness of technical and organizational measures for ensuring the security of processing. Further, the technology and methodology in the pilot meets security requirements, since pseudonymized data will be used. The pilot complies with the International Organization for Standardization (ISO) 27001 standards on information management security, and Hypertext Transfer Protocol Secure (HTTPS) is used for all connections.

The data collection in the periodic follow-ups will be conducted by a blinded research assistant. The data collection flow is shown in Fig. 1. The research assistant will write field notes after each contact with the participant to describe and understand the context.

The quantitative and qualitative data from the older adults and caregivers will be collected partly during home visits and partly through phone calls. Data from the informal caregivers will be collected through posted surveys if the caregivers do not live in the same household. Demographics from the participants and their caregivers, which will be collected consists of background data (age, comorbidities, type of housing, relationship to the older adult, employment, etc.). The participants’ health care resource consumption and their overall level or physical activity will be assessed at baseline, 3 and 6 months into the intervention (See Fig. 2).

Data collected from health care professionals will be collected through surveys and qualitative interviews at 2 weeks, 3 and 6 months into the intervention. The surveys consist of background data (age, education, number of working years, etc.) and structured questionnaires. The interviews will be conducted by a researcher focusing on the use of technology and the implementation processes.

All interviews conducted will be digitally recorded and transcribed verbatim. All identifying factors (e.g. names) will be deleted during transcription. Copies of the digital recordings will be destroyed after transcription has been completed. Interview transcriptions as well as quantitative data from the participants will be stored in the university’s database.

### Outcome measures

The different timepoints for the assessments are shown in Fig. 2.

#### Primary outcomes

The potential of the POSITIVE system on improving frailty will be assessed using *Linda Fried’s criteria* [4] and *FTS-5* [5] during a 6-month follow-up period. FTS-5 scores between 0 and 50. 0 is the best value and 50 the worst [5]. The two frailty scales correspond to the conceptual model of frailty phenotype, and in any case, the use of two scales could allow the performance of conducting a sensitivity analysis on the efficacy of the intervention on frailty measured in two different ways.

#### Secondary feasibility outcomes

Recruitment procedures, retention, and drop-out rates will be monitored continuously and registered throughout the study by the researchers. Compliance to the Vivifrail program for the IG will be evaluated through the registration in the physical exercise platform and for the CG through daily logbooks for exercises of the VIVIFRAIL guide. The influence of the context, the intervention level activities and the mechanisms of impact will be evaluated through monitoring process data, such as the level of daily use of the platform and conducting qualitative interviews with all participants from the IG (*n*=25) after the 6-month follow up, or until themes are saturated.

The usability and acceptance of the POSITIVE system will be asked using a questionnaire and will be collected by phone by the technical researcher from KTH.

Frailty transitions in prefrail and frail participants will be evaluated by *Fried’s Criteria* [4] and *FTS-5* [5]. The impact on locomotion in terms of changes in participants’ physical activity level and walking ability will be measured by *Short Physical Performance Battery (SPPB)* [36], *Gait Speed* [37] and *Timed Up and Go (TUG)* [38]. Participants’ independency level in ADL will be evaluated according to the *Barthel Index* [21, 31], *Katz-index* [39], *Lawton and Brody Index* [40] and *World Health Organisation Disability Assessment Schedule (WHODAS) 2.0* [41]. Given the inclusion criterion that establishes a Barthel index greater than 90, the target population is independent. Thereby in 6 months’ time, with the provided intervention, no modifications in the ADLs are likely to be observed. However, previous studies [21] demonstrate that this is sufficient time to see changes in the frailty status, which would imply, in case these changes are positive, a reduced risk to transition to disability.

The incidence of falls will be measured through *falls questionnaire* at baseline, which measures the number of falls pre-intervention, and 3 and 6 months into the intervention. The influence of the POSITIVE system on the cognitive functions will be measured by the *The Montreal Cognitive Assessment (MoCA)* [42] and the *clock drawing test* [43]. Changes in mood will be measured according to the *Geriatric Depression Scale (GDS- S)* [44]. Vitality will be addressed by measurements through *The Mini-Nutritional Assessment (MNA)* [45], and the instrument for assessment of the participant’s experienced quality of life will be *EuroQol-5D-5L* [46]. The participants’ perception of health and level of care received as well as involvement in care processes will be analysed by a questionnaire from *The International Consortium for Health Outcomes Measurement (ICHOM)*—Older person reference guide [47]. The usability and acceptance of the POSITIVE system will be evaluated by the *The System Usability Scale* (*SUS)* [48] and *Technology Acceptance Questionnaires*.

#### Caregivers and healthcare professionals

The caregiver’s quality of life and the caregiver burden will be measured by *EuroQol-5D-5L* [46] and *Caregiver Burden Scale* [49]. The economic impact on the caregiver will be investigated through an ad hoc questionnaire. The health care workers perspectives on the delivered intervention will be investigated by structured questionnaires related to the usability and acceptance of the technology and perspectives on the organisational model. The experienced workload will be measured by *the National Aeronautics and Space Administration Task Load Index (NASA TLX) questionnaire* [50].

### Data analysis

The potential efficacy of the POSITIVE-intervention will be analysed by an intention-to-treat method with a ‘per protocol analysis’, taking into consideration that the intervention group will be formed by those who do not have major technical problems, since this approach will portray better the use of the intervention in usual conditions at home. The participants will be analyed at different follow-up points to have information on some of those who will drop out later in the intervention process. For each follow-up visit, also the descriptive data will be presented as means and percentages. Linear and logistic mixed effects models will be used to assess the efficacy of the intervention and its impact on the measured parameters, to evaluate whether the objectives of the study are met or not. The one-tailed significance level will be set at *α*=0.05.

The qualitative data analysis will be performed from line-by-line transcription of the audios. The transcriptions will be coded by two researchers, and the data will then be merged into larger thematic categories, which will be discussed and compared by the researchers. The qualitative analysis will follow the content analysis process [51]. Results of the qualitative analysis will be reported at group level and individually, but information from individuals will not be identifiable. Comparisons between groups will be carried out.

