**Methods:**

The primary objectives are to estimate the potential efficacy of the POSITIVE system on improving frailty in at least one point in Fried’s criteria and five points in Frailty Trait Scale. The secondary objectives are to (A) assess the recruitment, retention, drop-out rates, compliance with the intervention and the intervention mechanisms of impact; (B) evaluate the usability and acceptance of the POSITIVE system, and to get estimations on; (C) the potential efficacy of the intervention on improving the participants’ physical performance, cognitive functions, mood, independency level in activities in daily living, the impact on quality of life and number of falls during the follow-up period; (D) the impact on the caregiver quality of life and caregiver burden; and (E) on the consumption of health care resources, participants’ perception of health and level of care received, and healthcare professionals’ workload and satisfaction.

A randomised controlled, assessor-blinded pilot study design recruiting from a primary care centre in Stockholm Region will be conducted. Fifty older adults identified as pre-frail or frail will be randomised into a control or an intervention group. Both groups will receive a medical review, nutritional recommendations and Vivifrail physical exercise program. The intervention group will receive the POSITIVE-system including a tablet, the POSITIVE application and portable measurement devices. The participants receiving the POSITIVE program will be monitored remotely by a primary care nurse during a 6-month follow-up. Data will be collected at baseline, 3 and 6 months into the intervention though the platform, standardised assessments and surveys. A process evaluation as per Medical Research Council guidance will be conducted after the 6-month follow-up period.

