### Participants

The eligibility/exclusion criteria for study participation can be seen in Table 1.

**Table 1 Tab1:** Eligibility and exclusion criteria

Eligibility criteria	Exclusion criteria
• Age ≥ 70 • Living at home • Having a caregiver/relative and/or supervision at home, or by a friend or partner, not necessarily living in the same building • Barthel Index ≥ 90 [29] • Have at least 1 criterion from Fried’s criteria	• Inadequate home infrastructure to host the required technology • Inability to understand how to use the POSITIVE system • Diseases that may affect prescription therapy: acute myocardial infarction in the last 3 months, unstable angina, aortic dissection, severe aortic stenosis, endocarditis/acute pericarditis, acute thromboembolic disease, acute heart failure, orthostatic hypotension (uncontrolled), recent fracture in the last month, terminal disease (< 12 months of life expectancy), other pathologies involving clinical instability • Psychiatric disorders that may potentially interfere in the clinical trial • History of alcohol/drugs abuse • Living with another participant, • Participating in other clinical studies • Three or more hospitalisations in the last year

To determine whether a participant can or cannot understand the use of the POSITIVE system, the participant will be asked to open the POSITIVE application in a tablet. Then the assessor will ask the participant to open different functions in the application and describe what they see. The caregivers’ and the health care workers’ perspectives on the POSITIVE system will be considered, and they will also be included as study participants.

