Lastly, even though the aim in this study is to have a cohort comparable to that of Spain and Poland which are part of the main POSITIVE project, the differences in the organisation of the health care system causes certain differences in the study processes and in the clinical praxis, and these should be considered when doing cross-cohort analysis in the main project.

Possible practical issues during the study may involve technical aspects, since many older adults may not be familiar with how to handle the technical equipment. However, a researcher from KTH will provide participants with support during the whole study, if needed. Another issue which may affect the study processes and participant recruitment is the current pandemic situation in the world, which in turn may negatively affect the recruitment of participants.

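### The efficacy analysis called intention-to-treat may leave out intervention-arm participants with major technical problems, a condition arising after randomisation in one arm only, so the estimate is likely, though not certainly, biased towards POSITIVE

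*Protocol article*

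**What the plan says.** Under Data analysis, the protocol article says that potential efficacy "will be analysed by an intention-to-treat method with a" per-protocol analysis. The same sentence goes on to say that "the intervention group will be formed by those who do not have major technical problems", and gives the reason: "since this approach will portray better the use of the intervention in usual conditions at home". The section does not say what makes a technical problem major, gives no corresponding rule for the control arm, and does not state which of the two populations is primary.

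Four other places bear on how this should be read:

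- **Who has the technology.** Abstract, Methods: "The intervention group will receive the POSITIVE-system including a tablet, the POSITIVE application and portable measurement devices". The control arm gets the medical review, nutritional advice and exercise programme without it.
- **When allocation happens.** Recruitment: "After the participant is enrolled, she/he will be randomised into the study". Use of the system at home comes later.
- **What is already screened.** Table 1, under Participants, excludes people from both arms before randomisation for "Inadequate home infrastructure to host the required technology" and "Inability to understand how to use the POSITIVE system".
- **What is expected during the study.** The Discussion foresees practical difficulties of a technical kind because "many older adults may not be familiar with how to handle the technical equipment".

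**The concern.** Improvement in frailty is the primary objective. If the analysed intervention group consists only of people whose system worked, while the control group keeps everyone, the comparison is no longer between randomised groups. Control participants who would have struggled with the equipment stay in. Their counterparts in the intervention arm may not.

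If people who run into technical trouble also tend to do worse on frailty, for example because they engage less, removing them raises the intervention mean without any effect of the system. The article says that the study should inform later powered trials, so an inflated estimate could make such a trial too small. It also plans a one-tailed test at 0.05 to judge whether the objectives are met, so the false-positive rate matters here even in a pilot.

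The stated reason is doubtful too. Technical problems are plausibly part of ordinary use at home. Leaving out the people who meet them describes use when the system works, which is a different question.

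**Working it through.** **Step 1: is this an eligibility rule or an analysis rule?** The two technical screens in Table 1 act before randomisation and on both arms. The sentence under Data analysis is placed with the analysis, refers to the intervention group alone, and is justified by how the system is used at home. Its natural reading is a further selection made after allocation.

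**Step 2: inputs.** From the article: 25 per arm (Sample size and power considerations) and a one-tailed level of 0.05 (Data analysis). The article gives no exclusion rate, outcome SD, or link between technical problems and outcome. All of these are assumptions below. There is no stated figure to reproduce.

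**Step 3: bias formula.** Suppose a share f of people in each arm is prone to major technical problems and their mean outcome is d SD worse. With no true effect, and the others at mean m:

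- control mean, everyone kept: m − f × d
- intervention mean, prone people removed: m
- spurious benefit: f × d

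The false-positive rates come from simulating trials of 25 per arm with a pooled t-test, 40,000 runs per row. A fresh run gave the bias shown and agreed with the error rates to within about 0.2 percentage points.

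| Share removed f | Deficit d | Bias f × d | One-sided error |
|---|---|---|---|
| 0.2 or 0.3 | 0 | 0 | about 5% |
| 0.2 | 0.5 SD | 0.10 SD | 9.4% |
| 0.3 | 0.5 SD | 0.15 SD | 11.7% |
| 0.2 | 1 SD | 0.20 SD | 15.4% |
| 0.3 | 1 SD | 0.30 SD | 22.2% |

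**Step 4: a second model.** Here the k intervention participants with the lowest score for technical ability are dropped, and rho is the correlation of that score with frailty improvement (50,000 runs, same test).

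| Dropped | rho | Bias | One-sided error |
|---|---|---|---|
| 5/25 | 0 | about 0 | 4.9% |
| 3/25 | 0.3 | 0.06 SD | 7.7% |
| 5/25 | 0.3 | 0.10 SD | 9.7% |
| 8/25 | 0.5 | 0.26 SD | 20.6% |
| 5/25 | −0.3 | −0.10 SD | 2.5% |

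Keeping all 25 as allocated gave 4.8–5.2% in every scenario.

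**Step 5: scale.** With 25 per arm and a one-sided 0.05 test, the effect detectable with 80% power is (1.645 + 0.842) × √(2/25) = 0.70 SD. A bias of 0.10–0.15 SD is about 14–21% of that.

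**Step 6: the one-point Fried target as a proportion.** Assume that 40% improve in both arms and that those dropped improve at 10%. Dropping 5 of 25 lifts the intervention rate to (0.40 − 0.20 × 0.10) / 0.80 = 47.5%, a false difference of 7.5 percentage points.

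**The case against.** The strongest reply is that the sentence describes two analyses. The restriction directly follows the words on per-protocol analysis, so it may belong to that one alone, with a conventional intention-to-treat analysis beside it. This reading is possible. A reader might infer that the plan definitely drops these participants and still calls the result intention-to-treat, but the wording does not settle that. What remains on either reading is that the two populations are merged, neither is named primary, and an unrestricted analysis is not promised.

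Second, the direction of bias is not documented. Once both arms have been screened for infrastructure and understanding, and with technical support offered throughout, the remaining problems could be device or connection faults with little bearing on prognosis. That makes a 1 SD deficit hard to assume, and zero or reversed bias is possible. Nor does the article say that those affected would be older or cognitively weaker. It mentions only lack of familiarity with the equipment.

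Third, a reader might take the Discussion to concede that technical failure belongs to usual home use. It does not. It speaks of practical issues during the study, and the criticism of the rationale is an inference from that.

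Fourth, it would go too far to say that the pilot hides technical failure. The section on secondary feasibility outcomes covers retention, drop-out, daily platform use, interviews with intervention participants, usability and acceptance. The gap is in the efficacy estimate.

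**Conclusion.** The point stands in a limited form. The efficacy paragraph permits an exclusion that follows randomisation and can touch only the intervention arm, under an intention-to-treat label. If applied, it breaks the comparability that randomisation gives, and the likely result is bias towards POSITIVE.

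The size is conditional throughout. It is nil if technical problems are unrelated to frailty outcome. A mild case gives about 0.06 SD with an error near 8%, and moderate assumptions give 0.10–0.15 SD with 9–12%. The figures of 0.20–0.30 SD and 15–22% need a 1 SD deficit and mark the severe end. A negative link reverses the sign. The stronger statement that the estimate is certainly biased in favour of the system is not supported, because the article has no data on that link. The need to reword does not depend on which scenario is true.

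**What to change.** Rewrite the paragraph in three parts.

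1. State that the primary efficacy analysis includes all randomised participants in the arm to which they were allocated, whether or not they had technical problems.
2. Move the restriction to a supplementary analysis labelled per-protocol. Define a major technical problem in advance, before outcomes are compared by arm, and acknowledge that the restriction applies to one arm only.
3. Report the number, type and timing of technical problems as a feasibility outcome, alongside the platform-use and usability measures already planned.

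A complier-average analysis with allocation as the instrument is optional. With 25 per arm it would be imprecise, and it assumes that allocation had no effect on those counted as non-users, which is doubtful if they had partial use or nurse contact.

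The cost is a rewording and, if technical problems are not already logged, a simple record of them. Design and sample size stay as they are. The effect estimate may come out somewhat smaller.

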## Methods

The primary objectives of the study are to assess the potential of the POSITIVE system on improving frailty by at least one point in Fried’s criteria and five points in Frailty Trait Scale-5 (FTS-5). The secondary objectives are (A) to assess the recruitment, retention, drop-out rates, compliance with the intervention as well as the intervention mechanisms of impact; (B) to evaluate the usability and acceptance of the POSITIVE system, and to get estimations on; (C) the efficacy of the intervention on improving the participants’ physical performance, cognitive functions, mood, independency level in activities in daily living (ADL), quality of life and the impact on number of falls during the follow-up period; (D) the impact on the caregiver quality of life and caregiver burden; and (E) on the consumption of health care resources, participants’ perception of health and level of care received and healthcare professionals’ workload and satisfaction.

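### Falls are recorded as a count, but the analysis section names only linear and logistic mixed models, neither of which gives a fall rate ratio (minor)

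*Protocol article*

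**What the plan says.** In the Methods section, secondary objective C of the protocol article includes "the impact on number of falls during the follow-up period". Under Secondary feasibility outcomes the same outcome is introduced as an incidence, "The incidence of falls will be measured through" a falls questionnaire, "which measures the number of falls pre-intervention, and 3 and 6 months into the intervention". So falls are a count, repeated over periods, and are described in terms that imply time at risk.

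The Data analysis section names the model families for all outcomes in one sentence: "Linear and logistic mixed effects models will be used to assess the efficacy of the intervention and its impact on the measured parameters". It adds that these models serve to judge whether the study's objectives are met, and "The one-tailed significance level will be set at" 0.05. It also says that participants will be analysed at the separate follow-up points so that later drop-outs still contribute, and that means and percentages will be given for each visit. No Poisson, negative binomial or other count model, and no exposure time, is mentioned.

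Objective E concerns effects "on the consumption of health care resources". The Data collection section says that this "will be assessed at baseline, 3 and 6 months into the intervention" but not whether it is recorded as visits, days or cost.

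**The concern.** The outcome and the named models do not match. A logistic model can answer whether a participant fell at all, but the objective asks how often. A linear model can compare mean counts, but its error assumption does not describe a variable that is mostly zero, skewed to the right and more variable where the mean is higher. Neither gives a rate ratio per unit of observed time or an estimate of overdispersion.

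The article's abstract and Discussion say that the study is meant to inform later powered studies. To plan one with falls as an outcome, the useful quantities are the control-arm rate, the overdispersion and a rate ratio with its interval. The planned per-visit means give an approximate control-arm rate. The other two would not come from the named models.

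**Working it through.** **Inputs from the article.** 25 per arm; 6 months of follow-up; falls asked about at baseline, 3 and 6 months; one-tailed α = 0.05; linear and logistic mixed models. The article states no fall rate, dispersion, drop-out rate or power, so there is no figure of its own to reproduce.

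**Assumptions.** Negative binomial counts with mean μ = 0.4 to 0.8 falls per 6 months and dispersion k = 1 to 2. Where an effect is assumed, the rate ratio is 0.5.

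**Step 1: shape of the count.** P(0) = (1 + kμ)^(−1/k); variance/mean = 1 + kμ.

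**Step 2: events lost by dichotomising.** Of μ expected falls per person, any-versus-none keeps 1 − P(0). The share lost is 1 − (1 − P(0))/μ.

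| μ | k | P(0) | Variance/mean | Share of falls lost |
|---|---|---|---|---|
| 0.4 | 1 | 1/1.4 = 0.714 | 1.4 | 1 − 0.286/0.4 = 0.29 |
| 0.4 | 2 | 1.8^(−1/2) = 0.745 | 1.8 | 1 − 0.255/0.4 = 0.36 |
| 0.8 | 1 | 1/1.8 = 0.556 | 1.8 | 1 − 0.444/0.8 = 0.44 |
| 0.8 | 2 | 2.6^(−1/2) = 0.620 | 2.6 | 1 − 0.380/0.8 = 0.53 |

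So 56% to 75% of participants have no fall, and a logistic analysis discards 29% to 53% of fall events.

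**Step 3: unequal variance under an effect.** Variance = μ + kμ². At rate ratio 0.5 with μ = 0.4, k = 1: 0.56 in controls against 0.20 + 0.04 = 0.24, a ratio of 2.3. With μ = 0.8, k = 2: 2.08 against 0.40 + 0.32 = 0.72, a ratio of 2.9.

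**Step 4: does the linear test fail?** Simulation with 25 per arm (1,500 runs per scenario, means 0.4 to 1.5, dispersion 0.5 or 1.5, drop-out 0 or 20% at the same rate in both arms) compared analyses of the 6-month total, a cross-sectional stand-in for the mixed models. With no true effect, the one-tailed error of the linear comparison was 0.043 to 0.057. It keeps its level. A Poisson rate model with robust standard errors and an offset gave 0.054 to 0.071, slightly above nominal.

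**Step 5: power at rate ratio 0.5.**
- Linear against rate model, complete follow-up, μ = 0.4 to 0.8 and k = 1 to 2: 0.24 to 0.40 against 0.26 to 0.42.
- Any fall against rate model, no drop-out, μ = 0.8 (20,000 runs): 0.24 to 0.33 against 0.32 to 0.41.
- At μ = 0.4 the gain over any fall depends on the variance estimator. A quasi-Poisson version showed none. The robust version in step 4 showed 5 to 10 points, but with the raised error noted there.

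**Step 6: does drop-out bias the result?** Suppose no true effect, and 30% of the intervention arm and 10% of controls leave at month 3 (assumed).
- Observed time is 0.70 + 0.30 × 0.5 = 0.85 against 0.90 + 0.10 × 0.5 = 0.95, so raw totals have a ratio of 0.85/0.95 = 0.89. The one-tailed error of a linear comparison of totals rises to about 7% to 8%.
- A linear comparison of mean falls per observed 3-month window, under the same exits, gave ratios of 0.997 to 1.001 and error of 0.050 to 0.055.

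The bias comes from counting a leaver's unobserved months as zero falls. It does not come from the linear model itself.

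**The case against.** The strongest defence is that the sentence on models is a generic line in a condensed article, that outcome-specific links and offsets usually sit in an SAP, and that falls are one of many secondary outcomes in a 50-person pilot with no power claim. This bears on severity. It does not remove the point, because the article does not leave the matter open: it names two families for the measured parameters, and neither suits the incidence that it sets out to measure.

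Three stronger readings are tempting, and the article does not support them.

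- *The linear test is invalid.* It is not: with equal arms its error stays near nominal (step 4) and its power is close to that of a rate model (step 5).
- *Unequal drop-out will make the intervention look protective.* That requires comparing totals without regard to time observed. The article plans mixed models and analysis at separate follow-up points. A participant who leaves after month 3 then has a missing month-6 value, not a zero. The near-nominal result for windows in step 6 assumes that exit is unrelated to falling and happens at the visit. Exit within a window would still leave some unequal exposure.
- *Health care use has the same fault.* The article never says that it is a count. If it were recorded as cost, it would be skewed but would not call for a count model.

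It is also fair to say that the planned per-visit means already give an approximate control-arm rate.

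**Conclusion.** The mismatch is real for falls, and minor. The logistic family answers a different question and discards about 29% to 53% of fall events under the assumed means and dispersions. The linear family gives a usable group test, but on an absolute scale and with a variance assumption that the outcome does not meet. Neither provides a rate ratio or a dispersion estimate.

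A count model would gain a suitable scale and interval, about 8 points of power over any fall at the higher assumed rate (0.24 to 0.33 becoming 0.32 to 0.41), and better planning inputs. It would not rescue an invalid test. All sizes rest on assumed fall rates and dispersions and on cross-sectional stand-ins for the mixed models. The primary frailty analysis is unaffected.

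**What to change.** Add one sentence to the Data analysis section: the number of falls will be analysed with a negative binomial or overdispersed Poisson (mixed) model, with log time at risk as offset and the pre-intervention fall count as covariate; the rate ratio with 95% CI and the dispersion estimate will be reported as exploratory, and any fall will be given as a descriptive percentage. Use the same model for health care use only where an item is recorded as a count.

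The 95% interval is for estimation and does not mirror the one-tailed 5% test; saying so avoids confusion.

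The cost is close to nil. Falls are already counted at each visit, and time at risk should be obtainable from the drop-out monitoring described under Secondary feasibility outcomes. There are two small downsides: dispersion is poorly estimated with 50 people, and the count model's type I error may be slightly above nominal (0.054 to 0.071 with robust standard errors), which is a further reason to label the results exploratory.
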